### Surgical technique

The RAMPS procedure is based on a report by Strasberg et al. (8, 9). All surgeons and their surgical teams are skilled in performing this procedure. To optimize for the best outcome, surgeons can decide to perform anterior or posterior RAMPS based on their evaluation of certain clinical cases during the surgery. Meanwhile, tiny variations in lymph node dissection and necessary extended tissue or organ resection, which are not beyond the guideline, are allowed (8, 9, 20, 21). In the MI-RAMPS group, all surgical teams can choose the appropriate general laparoscopic method or robotic techniques, such as the da Vinci^®^ Surgical System, according to their preference and availability of resources.

### Conversion

Conversion is defined as any case requiring additional hand-assisted approaches, except those for trocars and specimen collection, in the MI-RAMPS group (22, 23). Based on practical scenarios, the conversion will consist of reactive conversions (such as bleeding and organ perforation) and conditional conversions (such as difficult exposure, failure to proceed, and expanded tumor evasion) (22). The details about the conversion will be recorded for future analysis. According to the principle of intention-to-treat, patients who will undergo conversion will be continually analyzed in the MI-RAMPS group.

### Blinding

The MIRROR trial is an open-label trial. However, several approaches will be applied to minimize the interference of subjective factors in the study findings. For example, patients will provide informed consent for both approaches and the study. However, they will be blinded to their specific groupings during the treatment. After the treatment, patients will not be actively informed of the specific surgical steps and procedures. The patient, however, reserves the right to know or quit anytime. Neither the pathologists involved in the postoperative evaluation nor the adjudication committee will be informed of treatment assignments.

### General treatment regimen

The strategy and protocol of the general treatment during the perioperative period for both MI-RAMPS and O-RAMPS groups are the same. They include prophylactic drainage, nutritional support, anti-infection, proton pump inhibitor use, somatostatin use, blood sugar management, pain management, deep vein thrombosis prevention, and existing disease management. Other treatments, such as interventional therapy and reoperation, will be performed, if necessary, for the management of severe complications after the surgery.

### Primary outcome

The primary outcome is the postoperative length of stay (LOS). Experienced surgeons will be responsible for the approval of discharge based on uniform criteria (24), including (i) no need for IV fluid; (ii) performance status and organ function recovery to the preoperative state; (iii) solid diet availability; (iv) no sign of infection; and (v) acceptable incision healing and pain control. However, discharge criteria do not include prophylactic drainage removal.

Patient evaluation will be recorded on case report forms (CRF) based on the observation and medical records for every round. Once the patient is eligible for discharge, the investigator will record the condition and date for the calculation of LOS, regardless of the similarity of the actual discharge date, as it may be affected by certain non-medical factors. If the evaluation for some cases is controversial, the senior surgical adjudication committee will be consulted.

### Secondary outcomes

The secondary outcomes of the MIRROR study include surgical outcomes, complications, pathological outcomes, time and rate of return to adjuvant therapy, and long-term survival.

### Surgical outcomes and complications

The details during the surgery will be recorded, including procedure type, surgical team, surgery duration, estimated blood loss, transfusion, conversion, combined vessel, and/or organ resection. To evaluate the quality of life, the VAS score, QLQ-C30, and QLQ-PAN26 will be used postoperatively.

Additionally, the rate of major complications and their detailed management will be recorded and investigated. Major complications will be defined according to the Clavien-Dindo grade III-IV classification system (25). Common complications after pancreatic surgery, such as postoperative pancreatic fistula, delayed gastric emptying, and hemorrhage, are classified based on the International Study Group on Pancreatic Surgery (ISGPS) guidelines (26–29). Only Grade B and C pancreatic fistula will be identified.

### Pathological outcomes

All specimens will be collected for lymph node sorting, incision margin marking, and labeling by surgical team members (under the supervision of seniors or operators) and then sent to two pathologists for evaluation. R0 resection rate is one of the crucial secondary factors. R0 resection is recognized when the distance between the margin and tumor is >1 mm. R0 resection will be mainly evaluated using either the transection margin or retroperitoneal margin. Multiple pathological factors, such as the number of lymph node harvests, number of positive LN, LN ratio, and status of margin, will be recorded and analyzed if detectable (30). TNM staging according to the American Joint Committee on Cancer (AJCC) classification (8th edition) will be recorded (31).

### Long-term survival

Disease-free survival (DFS) and overall survival (OS) will be used as secondary outcomes of this study. DFS is the postoperative survival period without recurrence and metastasis of the primary tumor. OS is defined as the entire length of survival after the RAMPS procedure. All related survival information, including recurrence, metastasis, and survival status, and the subsequent anti-cancer treatment information will be acquired during the postoperative follow-up. The anticipated mean follow-up period for the survival study is 24 months.

### Patient follow-up

The follow-up plan consists of out-patient clinic visits 1, 3, and 6 months after the surgery. Thereafter, patients will be followed up every six months. In case of a no-show in the clinic, the interview by phone will be conducted at every interval. Detailed information on symptoms, lab tests, medical imaging examinations (ultrasound, CT, MRI, or PET-CT), adjuvant therapy regimen, recurrence, metastasis, and survival status will be recorded at every follow-up visit.

### Data collection

All data of enrolled patients will be gathered into a central database, the Electronic Data Capture (EDC) system, based on the previous design of the CRF, which consists of baseline information, randomization result, lab test result, medical examination, surgical treatment information, peri-operative management record, and follow-up data. To secure quality and confidentiality, all data will be under surveillance by a third-party professional data management team.

### Quality and safety

All participating centers and their surgical teams are experienced in RAMPS procedures and other pancreatic surgical procedures. Each center has at least one senior surgeon who will join the surgical adjudication committee, comprising seniors from other centers, to ensure safety and procedure standards. All the senior surgeons are specialists in pancreatic surgery and will be available for assessment and consultation for difficult cases during the trial.

Regarding histopathological evaluation, all specimens, including primary tumor and resected lymph nodes, will be collected and marked (such as resection margin) by the surgical team before transfer to the pathological team. At least two expert pathologists will evaluate every case, one being a senior specialist in hepatopancreatobiliary (HPB) disease diagnosis. If the assessment is inconsistent with that of the other pathologist, another HPB pathologist will be invited for final evaluation.

### Ethics

This trial will be conducted according to the principles of the Declaration of Helsinki (32). The study protocol has been received and approved by the Institutional Review Board (IRB) of Peking Union Medical College Hospital (No. ZS-1823). Additionally, approval was obtained according to the local regulations of all participating centers. The trial has been registered on Clinicaltrials.gov (NCT03770559).

### Statistics

#### Sample size calculation

The MIRROR trial has been designed as a superiority trial. We hypothesize that patients with distal pancreatic cancer who undergo MI-RAMPS have a shorter postoperative stay than those who undergo O-RAMPS. Based on our previous experience and related data on the retrospective cohorts (15, 16), the expected superiority in the length of stay in the MI-RAMPS group is 3 ± 8 days. These factors, 5% two-sided significance level (α), 80% power (1-β), and 10% drop-off rate, were considered in calculating the sample size. Accordingly, the expected sample size has been set at 250 patients (125 patients in each group).

#### Statistical analysis

Continuous variables will be expressed as means with standard deviation or median and compared using the independent samples T-test and Wilcoxon rank test. Categorical variables will be described as percentages and compared using the Pearson Chi-square test, continuity correction, or Fisher’s exact test. Survival will be evaluated using both OS and DFS. Clinically considerable or significant variables based on univariate analysis will be included in multivariate analysis, which will be performed by Cox regression analysis. P-value <0.05 will indicate statistical significance.

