### Randomization

Eligible participants will be recruited from eight centers after providing written informed consent. Stratified blocked randomization between O-RAMPS and MI-RAMPS will be performed in a 1:1 ratio; Before randomization, patients will be assigned to two subgroups based on resectability: borderline resectable subgroup and resectable subgroup to perform independent stratified randomization. Patients identified as borderline resectable, as illustrated in “borderline resectable tumor,” will be assigned to borderline resectable subgroups. Otherwise, the case will be in the resectable group for randomization. The block sizes will be subjected to random variation. Randomization will be concealed from all investigators. Patients will be assigned codes by numeric randomization coding, and the study coordinator will be the only one with access to these codes. The source data will be stored digitally and kept in the central database. Randomization will be performed after the surgical plan is made and the written informed consent from patients and approval for the trial are available. Patients who rescind their decision to undergo surgery and those who do not undergo surgery will be excluded from the analysis.

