In this trial, RAMPS will be performed using either the anterior or posterior approach according to the scope of surgical resection, which is mainly selected according to the intraoperative assessment of the chief surgeon. However, we stratified resectability before randomization because of significant differences in treatment strategy and prognosis between patients with resectable and borderline resectable tumors. A common criterion for assessing resectability is vascular invasion. However, Isaji et al. (18) have proposed certain biological criteria (CA19-9) and performance status evaluation, which have been adopted in this study. Moreover, the MIRROR trial will include a strict pathological evaluation system to reflect the oncological outcomes of MI-RAMPS. Concerning the pathology report evaluation, we will follow the margin evaluation system proposed by the Japan Pancreas Society (30) and TNM staging by AJCC to evaluate the margins, lymph nodes, and suspicious invasion in multiple dimensions to ensure the diagnostic accuracy of the pathology report.

The primary outcome of this study will be the length of postoperative hospital stay. LOS could directly and better reflect the period between operation and postoperative adjuvant therapy. In this study, all participating centers and their pancreatic surgical teams are well-experienced in both O-RAMPS and MI-RAMPS, as well as general peri-operative management. Moreover, each center has assigned at least one senior pancreatic specialist to join the adjudication committee for supervision and consultation. Therefore, to a certain extent, we believe that based on accurate evaluation criteria, the results of the corresponding superiority of LOS will indicate that MI-RAMPS is beneficial for enhanced postoperative recovery. By validating this hypothesis, we expect to provide distal pancreatic cancer patients with a safe, minimally invasive way to get the tumor radical removal and receive the necessary postoperative adjuvant therapy timely for the best chance of survival.

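### The length-of-stay comparison ignores the resectability strata used to randomise and does not say which of two named tests decides superiority

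*Protocol article*

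**What the plan says.** The Randomization section of the Protocol article divides patients into a "borderline resectable subgroup and resectable subgroup to perform independent stratified randomization", with 1:1 blocked allocation. Resectability is the only stratification factor named; the eight centres are not one. The Discussion gives the reason: "we stratified resectability before randomization because of significant differences in treatment strategy and prognosis between patients" with resectable and with borderline resectable tumours.

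The primary outcome is postoperative LOS, counted to the date on which uniform discharge criteria are met. The Sample size calculation section works on the mean scale: "the expected superiority in the length of stay in the MI-RAMPS group is 3 ± 8 days", with "5% two-sided significance level (α), 80% power (1-β), and 10% drop-off rate", giving 250 patients, 125 per group.

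The Statistical analysis section has no sentence specific to LOS. For continuous variables as a class it says: "Continuous variables will be expressed as means with standard deviation or median and compared using the independent samples T-test and Wilcoxon rank test". The threshold of P below 0.05 is tied to neither test. The only multivariable model mentioned is Cox regression, in the context of survival.

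**The concern.** Two things are fixed badly for the outcome on which the trial will be judged.

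First, stratified randomisation balances the arms on resectability by design. An unstratified test leaves the variation between strata in its error term, as if that balance had arisen by chance. If resectability predicts LOS, the standard error is too large, the test runs below its nominal 5%, and power that the design has already paid for is not used.

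Second, two tests are joined with no rule for choosing between them. LOS is usually right-skewed, and on skewed data a t-test and a rank test can reach different conclusions. A reader of the final report could not tell from this text which P-value was meant to decide the hypothesis.

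**Working it through.** **1. The plan's own figure.** Inputs from the Sample size calculation section: difference 3 days, SD 8 days, two-sided 5%, 80% power, 10% drop-off.

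- n per arm = 2 × (1.960 + 0.842)² × 8² / 3² = 111.6, so 112.
- With drop-off: 112 / 0.9 = 124.4, so 125 per arm and 250 in total.

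This matches exactly. A t-based calculation gives 113 per arm and 126 after drop-off, practically the same. The sample size is not at fault.

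**2. Share of LOS variance explained by resectability.** The article does not give it, so it is assumed. With a fraction p of borderline patients and a gap of D days between strata, R² = p(1 − p)D² / 64. For p = 0.30:

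- D = 3: 0.21 × 9 / 64 = 3.0%
- D = 5: 0.21 × 25 / 64 = 8.2%

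**3. Effect of ignoring the strata.** Let d = 3 / (8 × √(2/112)) = 2.806. For a factor balanced by design:

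- true level of the unadjusted test = 2 × [1 − Φ(1.96 / √(1 − R²))]
- power of the unadjusted test = Φ((d − 1.96) / √(1 − R²))
- power of the adjusted test = Φ(d / √(1 − R²) − 1.96)

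| R² (assumed) | True level, unadjusted | Power, unadjusted | Power, adjusted |
|---|---|---|---|
| 0% | 5.0% | 80.1% | 80.1% |
| 3% | 4.7% | 80.5% | 81.3% |
| 8% | 4.1% | 81.1% | 83.3% |

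The power given up is 81.3 − 80.5 = 0.8 points at R² = 3%, and 83.3 − 81.1 = 2.2 points at R² = 8%.

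Simulation (8,000 trials per scenario, 224 evaluable patients, blocks of 4 or 6 within resectability, normal or log-normal LOS, total SD 8) agrees in direction. With a 5-day gap the unadjusted t-test rejected in 3.5% to 4.1% of null trials. Simulation error is about 0.25 points on the level and 0.45 points on power.

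**4. Centre.** In the same simulations, with centre explaining 10% of LOS variance (assumed) and no stratum effect:

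- power was 79.6% to 79.9% unadjusted and 82.4% to 82.5% with resectability and centre in the model, a gain of about 3 points;
- the level of the unadjusted t-test stayed at 4.8% to 4.9%.

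With no centre effect, adding centre lowered power from 79.5% to 78.3% (normal) and from 79.7% to 78.1% (log-normal), a little over 1 point.

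**5. Two tests, no rule.** Under the null with no stratum or centre effect, at least one of the two tests was significant in 6.2% (normal) or 7.0% (log-normal) of trials. At the planned 3-day effect the two disagreed on significance in about 5% of trials with normal LOS and 10% to 14% with log-normal LOS.

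**The case against.** The strongest reply is about scope. The Statistical analysis section is a short summary for all continuous variables in a journal article. A full analysis plan may well settle covariates, centre and the choice between a parametric and a rank test. The wording can also be read as pairing mean with t-test and median with Wilcoxon according to distribution. Part of this stands: the full plan may already resolve the point. But the article does more than stay silent. It names the tests, names none that uses its own strata, and governs LOS through that sentence alone. Even the charitable reading would let the data choose the primary test unless a rule is fixed in advance.

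Four stronger readings are tempting, and the documents do not support them.

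- *The trial is underpowered.* It is not. The unadjusted t-test keeps the planned 80%; the loss is only relative to an adjusted analysis.
- *Leaving out centre also makes the test conservative.* It does not, because centre is not a named stratum. Large conservatism would need resectability alone to explain far more of LOS variance than a 3- to 5-day gap implies.
- *The Discussion shows that centres differ in discharge time.* Its remark concerns differences between countries and explains why the trial is not international. The uniform discharge criteria, applied regardless of the actual discharge date, work against centre differences.
- *Type I error is inflated.* That holds only under an either-test rule, which the article never states. Ignoring the strata pushes the other way: with a 5-day gap, the either-test rate in the simulations was 4.2% to 5.4%.

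Nor can a fixed power advantage be claimed for the Wilcoxon test. With log-normal LOS and a 3-day mean difference, its simulated power ranged from about 83% under proportional shortening to well above 90% under a pure shift.

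**Conclusion.** The point holds in a limited form. The stated analysis of the primary outcome does not follow the stratified design and leaves open which test decides superiority.

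For resectability explaining about 3% to 8% of LOS variance, the cost is a true level of about 4.7% to 4.1% and about 1 to 2 power points. That range rests on an assumed 30% borderline patients and an assumed gap of 3 to 5 days. The stated reason for stratifying refers to treatment strategy and prognosis, not to LOS, so the true share could be smaller. Omitting centre might cost about 3 further points if it explains 10% of variance, which is also assumed.

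The open choice of test matters more for credibility than for any single figure. The 6% to 7% error is what an either-test reading would give without a stratum effect; it is not a rule that the plan adopts. The sample size stands. The change is worth making because it is nearly free.

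**What to change.** In the Statistical analysis section, add a sentence specific to LOS:

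- **Primary analysis:** one two-sided 5% test of the mean difference between arms, from a linear model with arm and resectability, reported with its 95% confidence interval. This stays on the scale of the 3-day difference that sized the trial.
- **Centre:** may be added as a covariate. State the decision in advance; it costs about 1 power point if centre has no effect.
- **Sensitivity analysis:** a Wilcoxon test stratified by resectability. A rank test stratified by both resectability and centre would have 2 × 8 = 16 cells, averaging 224 / 16 = 14 evaluable patients. With centre not balanced by design some cells could be lopsided, so it is not a natural primary choice.

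If a full analysis plan already fixes one primary test, the article's wording need only be aligned with it. As the trial is described as open-label, the wording should be settled before outcome data are examined by arm. Resectability is known at randomisation and centre is known for every patient, so nothing new is collected and N stays at 250. The cost is analysis wording only.

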**Conclusion:**

This study will offer a relatively higher level of evidence to further illustrate the accessibility and benefits of MI-RAMPS for the treatment of distal pancreatic cancer.

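### One flat P<0.05 rule covers LOS and every secondary comparison, although the 5% level was set for LOS alone; a low-severity wording point that one sentence fixes

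*Protocol article*

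**What the plan says.** The protocol article names one primary outcome, LOS. Its Sample size calculation section states the hypothesis for LOS only, with the planning values "the expected superiority in the length of stay in the MI-RAMPS group is 3 ± 8 days" and "5% two-sided significance level (α), 80% power (1-β), and 10% drop-off rate".

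The Secondary outcomes section then sets out five domains: "The secondary outcomes of the MIRROR study include surgical outcomes, complications, pathological outcomes, time and rate of return to adjuvant therapy, and long-term survival". The sections that follow fill these in with operative details, quality-of-life scales, complications, pathology and survival. On pathology, the article says "R0 resection rate is one of the crucial secondary factors".

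The Statistical analysis section names tests for continuous and categorical variables and Cox regression for the multivariate analysis. It ends with a single threshold: "P-value <0.05 will indicate statistical significance". The sentence does not separate primary from secondary outcomes.

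**The concern.** The significance level was chosen for one test, and the analysis section then uses it as the definition of significance for all tests. Followed literally, an isolated P-value just under 0.05 on blood loss, node harvest, a fistula rate, R0 or disease-free survival would carry the same label as the LOS result, even if LOS showed no difference.

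This has some practical weight because the article's stated interest goes beyond LOS. The abstract's conclusion says "This study will offer a relatively higher level of evidence to further illustrate the accessibility and benefits of MI-RAMPS", and the Discussion describes the trial as an investigation of safety and efficacy. Safety, margins, nodes and survival are all secondary here. The rule works in both directions: a chance harm would be labelled significant as readily as a chance benefit.

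**Working it through.** **1. What the 5% belongs to.** Inputs from the Sample size calculation section: difference 3 days and SD 8 days (reading 3 ± 8 as difference ± SD), two-sided α 0.05, power 0.80, drop-off 10%.

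n per arm = 2(z₀.₉₇₅ + z₀.₈₀)² × SD² / difference² = 2 × (1.960 + 0.8416)² × 64/9 ≈ 111.6, so 112.

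With drop-off: 112 / 0.9 = 124.4, so 125 per arm and 250 in total. This matches the article: "the expected sample size has been set at 250 patients (125 patients in each group"). The 5% is therefore the level of the single LOS comparison.

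**2. How many secondary comparisons.** The article gives no count. My reading of the sections from Secondary outcomes to Long-term survival is:

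| Group | Comparisons | Number |
|---|---|---|
| Operative | duration, blood loss, transfusion, combined vessel/organ resection | 4 |
| Quality of life | VAS, QLQ-C30, QLQ-PAN26 | 3 |
| Complications | major complications, pancreatic fistula, delayed gastric emptying, hemorrhage | 4 |
| Pathology | R0, nodes harvested, positive nodes, node ratio | 4 |
| Adjuvant therapy | time to, rate of | 2 |
| Survival | DFS, OS | 2 |
| **Total** | | **19** |

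Conversion is left out because it exists in the MI-RAMPS arm only. Each questionnaire counts once, and margin status is taken as overlapping R0. Adding margin status and TNM stage gives 21. The lowest reading is one test per listed domain, which is 5.

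**3. Expected number of chance results.** With every null true, the expected number below 0.05 is 19 × 0.05 = 0.95, whatever the correlation. For 5 tests it is 5 × 0.05 = 0.25.

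**4. Chance of at least one.** If the tests are independent, it is 1 − 0.95^m:

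- m = 19: 1 − 0.95¹⁹ = 0.623
- m = 5: 1 − 0.95⁵ = 0.226

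For correlated tests, assume normal test statistics with a common pairwise correlation ρ, and condition on the shared factor u. Each test stays inside ±1.96 with probability

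p(u) = Φ((1.96 − √ρ·u)/√(1−ρ)) − Φ((−1.96 − √ρ·u)/√(1−ρ)).

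The chance of at least one false positive is 1 − ∫ p(u)^m φ(u) du, integrated numerically:

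| Assumed ρ | m = 19 | m = 5 |
|---|---|---|
| 0 | 0.62 | 0.23 |
| 0.3 | 0.53 | 0.21 |
| 0.5 | 0.41 | 0.18 |
| 0.7 | 0.28 | 0.15 |
| 0.8 | 0.22 | 0.13 |

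**5. The primary test.** LOS is a single named outcome tested at two-sided 5%. The number of secondary tests does not change its error rate.

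**The case against.** The case against is substantial, and most of it stands.

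- **Unseen documents.** Rules for multiplicity among secondary outcomes are commonly set in a full protocol or statistical analysis plan. Neither is shown, so the absence of a hierarchy or an adjustment is not a fault of this article. What remains is the sentence that the article does state, which makes the threshold universal. If another document restricts it, the published sentence misdescribes the plan; if none does, it applies as written.
- **LOS is kept apart.** It is the only primary outcome, the only one with a hypothesis and a power calculation, and the Discussion rests its conclusion about recovery on LOS. A reader might infer that the trial's main conclusion is exposed to inflated error, or that the plan lets a secondary outcome rescue a failed primary. The documents support neither: the LOS error is not inflated, and no confirmatory claim from a secondary is promised.
- **No stated error rate is breached.** It is tempting to set 0.41 or 0.62 against the 5% and call it a multiple of the planned error. The article never claims family-wise control over the secondaries, so that comparison has no stated benchmark.
- **A single headline figure would be misleading.** The 41% needs a common correlation close to 0.5, which the article does not give. The count of 19 is also a reading: the article says that operative details are to be recorded and the scales used, not that each will be formally tested.
- **R0 is still called secondary.** The article's emphasis on R0 does not make it a co-primary outcome.
- **Harms.** Adjusting or suppressing tests on complications would make harms harder to see. This limits what the fix should do.

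**Conclusion.** The point holds as a low-severity matter of wording. The analysis section states one significance rule for everything, while the level it uses was set for LOS alone. On a reading of 19 secondary comparisons, all truly null, about one (0.95) would be expected to be labelled significant by chance. The probability of at least one ranges from 0.22 to 0.62 for common correlations from 0.8 down to 0. On the narrowest reading of five tests, the range is 0.13 to 0.23.

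These figures rest on three assumptions: the count, an equal pairwise correlation, and every secondary null being true. The conclusion does not depend on any one value, since a chance secondary finding is far from rare under every case shown. The sample size and the LOS analysis need no change on this account.

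**What to change.** Replace the last sentence of the Statistical analysis section with wording such as:

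*Statistical significance (two-sided P<0.05) applies to the primary outcome, LOS. Secondary outcomes, including R0 resection, DFS and OS, are exploratory and are reported as between-group estimates with 95% confidence intervals. Any P-values given for them are nominal and unadjusted for multiple comparisons. Complications are reported in full, without adjustment.*

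If a statistical analysis plan already sets a hierarchy for some secondary outcomes, the sentence should point to it instead.

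The cost is one sentence in the plan and matching labels in the report. Data, sample size and the primary test stay as they are. The small downside is that an isolated secondary P<0.05 can no longer be presented as a significant benefit. Leaving complications unadjusted and fully reported keeps possible harms visible.
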